### 6.3 FURTHER MEASUREMENTS

- Adherence to the study intervention is only observed in the M-sense Migräne app group and on weekly basis. Being adherent is defined for a patient as using an app feature which is not implemented in the control app, at least one time per week.
- Tracked usage of app features during the 12 weeks is only measured in the intervention group with M-sense Migräne including (a) Headache reporting and attack classification diary; b) Medication intake diary; c) Trigger factors diary; d) Analysis function and physician report; e) Personalized education on disease- and trigger management; f) Relaxation therapy; g) Training module; h) Acute pain therapy. This data will be displayed descriptively.
- Concomitant activities/ activities are documented in both groups (activities recorded in an app diary: mindfulness practice, breathing meditation, autogenic training, muscle relaxation, qigong/tai chi, yoga, nordic walking, cardio-training, fitness course, running, cycling, and swimming) used against headache during the first 12 weeks (activity, and time spent for respective activity). Some of these activities are recommended in the app, others not. We will calculate the number of patients with respective activities.

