## 10.4 HANDLING DROPOUTS AND MISSING DATA

### 10.4.1 Dropouts intervention group

Dropouts in the intervention group (randomized to the M-sense Migräne app) are defined as patients who are **not** answering the daily headache question at least 3 days per week for at least 4 weeks consecutively OR have been non-adherent to the intervention for at least 4 weeks consecutively (please see definition for adherence 6.3.). We distinguish between study dropouts and intervention dropouts and will employ different methods to handle missing data for the different types of dropouts in the group with the M-sense Migräne app.

- Intervention dropout are non-adherent for at least 4 consecutive weeks, BUT answer the daily headache question at least 3 days per week during the weeks of non-adherence. For this group missing data will only be imputed for the weeks where missing data was detected according to the missing data definition (see 10.4.3).
- Study dropouts decline further participation OR are **not** answering the daily headache question at least 3 days per week at least 4 weeks consecutively OR are non-adherent for at least 4 weeks consecutively, but are **not** answering the daily headache question at least 3 days per week during the weeks of non-adherence. For this group missing data will be imputed based on data from the control group using reference-based multiple imputations, applying a copy increments in reference procedure. We will use the so-called copy increments in reference (CIR) procedure. In the CIR procedure the intervention group's imputed outcomes after dropping out from the study mimic (parallel) the gradient from the control group.
- For sensitivity analyses we will use multiple imputations based on data of the entire data set, because we assume that patients dropping out will have already treatment benefits, because this has been observed in available data from M-sense Active. Therefore, this procedure also reflects a conservative approach. Multiple imputations based on the data of the intervention dropouts will not be considered as sensitivity analyses, because we expect this group to be too small for a robust multiple imputation procedure.

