### 10.4.3 Missing Data

Data completeness in the diary will be considered on a weekly basis and data are defined as missing if the daily headache question has not been answered at least 3 days per week during a respective week. Missing data for the diary will be imputed on the week-level. Missing data in questionnaires, will be imputed based on the measurement time point. For missing data imputation a multiple imputation procedure will be used (regression based multiple imputation method stratified by treatment group and type of disease (chronic or episodic migraine) with five imputed datasets.

Imputation model: imputations for continuous data will be generated with the predictive mean matching method (pmm). The following variables will be used as predictors in the imputation process for missing values at later time points: headache days, migraine days, age, gender, education level, duration of migraine disease, quality of life (HIT-6), self-efficacy (HMSE-G-SF), headache attributed burden (HALT-30), and migraine-specific health literacy.

In case the respective information for the classification of the headache days into migraine days, days with tension type headaches and other headaches has not been documented, we will use a conservative approach and assume a migraine day. Therefore, we will replace these missing values with migraine days in both groups, for the intervention phase as well as for the baseline phase.

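### The app-arm imputation model in SAP 10.4.3 leaves out weekly adherence, so the few missing weeks that escape the control-based rule are pulled towards on-app values

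*Combined protocol and SAP*

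**What the plan says.** SAP 10.4.3 works by diary week: "data are defined as missing if the daily headache question has not been answered at least 3 days per week during a respective week". Such weeks are filled by a "regression based multiple imputation method stratified by treatment group and type of disease (chronic or episodic migraine) with five imputed datasets", using predictive mean matching. A sentence that opens "The following variables will be used as predictors in the imputation process for missing values at later time points" then lists the diary counts, demographic items, time since onset and four questionnaire measures. Nothing on app use appears.

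SAP 6.3 records adherence weekly in the app arm and defines it as "using an app feature which is not implemented in the control app, at least one time per week". A week with no such use is non-adherent whether or not the diary was answered, so the status is known for weeks whose diary is missing.

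SAP 10.4.1 splits app-arm dropouts in two:

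- **Study dropouts** decline further participation, leave the diary for at least four consecutive weeks, or are non-adherent for at least four consecutive weeks without keeping the diary in them. They are imputed from the control group by copy increments in reference (CIR).
- **Intervention dropouts** are "non-adherent for at least 4 consecutive weeks, BUT answer the daily headache question at least 3 days per week during the weeks of non-adherence". Their rule is: "For this group missing data will only be imputed for the weeks where missing data was detected according to the missing data definition".

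App-arm patients who meet neither definition fall to the general model in 10.4.3.

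**The concern.** Under the intention-to-treat analysis, observed weeks after a patient stops using the app count as they are. A missing off-app week should therefore be imputed as an off-app week. The 10.4.3 model cannot do this, because nothing in it tells a week off the app from a week on it. Donors come from the same arm and migraine type, and most are presumably still using the app.

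Stopping use plausibly makes a missing diary week more likely. If the app works and the benefit fades, it also raises the migraine count in that week. A logged variable linked to both missingness and outcome is then left out of one arm's model, and the error goes in one direction, towards the app. It enters the only confirmatory test, and none of the sensitivity analyses in SAP 10.5.2 adds adherence to the imputation.

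**Working it through.** **1. Which missing app-arm weeks reach the within-arm model?**

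| Pattern | Rule |
|---|---|
| Declines participation, or diary left for 4+ consecutive weeks | CIR from control |
| Non-adherent 4+ weeks, diary not kept in them | CIR from control |
| Non-adherent 4+ weeks, diary kept in all of them | Those weeks are observed, so no imputation |
| Non-adherent 4+ weeks, diary kept in some of them | Not settled by 10.4.1: CIR or within-arm |
| App and diary both stopped silently from week 10 or later | Within-arm |
| Off-app gap of 1 to 3 weeks | Within-arm |

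The fifth row follows by counting. From week 10 only weeks 10, 11 and 12 remain, which is three, and the dropout rules need four consecutive weeks. Up to three of the four endpoint weeks can then be imputed within the arm.

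**2. The plan's own figures.** Inputs from SAP section 7: difference 1.69 − 0.42 = 1.27, SD 4.20, two-sided alpha 0.05, power 80%.

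- Normal approximation: n = 2 × (1.960 + 0.842)² × 4.20² / 1.27² ≈ 171.7, so 172 per group.
- Exact t-test: 173 per group, power 80.1%. The stated 173 reproduces.
- Standard error: 4.20 × √(2/173) = 0.45 days, before any gain from baseline adjustment.

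**3. Ceiling on the shift.** Let f be the share of the app arm with off-app missing weeks outside CIR, m the number of those weeks in weeks 9 to 12, and L the effect lost on stopping, in days per 28. If these weeks are imputed entirely at the on-app level, the shift is f × (m/4) × L. The documents give none of f, m or L, so these are assumed ranges. With L = 1.27:

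- f = 5%: 0.05 × 1/4 × 1.27 = 0.016 (m = 1) to 0.05 × 3/4 × 1.27 = 0.048 (m = 3)
- f = 10%: 0.032 to 0.095
- f = 20%: 0.064 to 0.191

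Half loss (L = 0.635) halves each value.

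**4. Simulation of late silent stopping.** App arm of 173, app stopped at week 10, half of the stoppers also silent from week 10, 5% other missing weeks, predictive mean matching, no split by migraine type. With full loss of effect, the shift was 0.045 days at 10% stopping and 0.086 at 20%. The matching ceilings are 0.10 × 0.5 × 3/4 × 1.27 = 0.048 and 0.20 × 0.5 × 3/4 × 1.27 = 0.095. The shift is close to the ceiling because all earlier diary weeks were on the app and carry no sign of stopping. Across half to full loss at 10 to 20% stopping, the range is about 0.02 to 0.09. With an off-app indicator it is about zero.

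**5. Simulation of partly kept diaries.** Off the app from week 5, half of these patients with one to three missing weeks from week 9, full loss, regression imputation within the arm. The shift was 0.010 to 0.031 days at 10% off the app and 0.019 to 0.055 at 20%. That is about 60% of the ceiling, because observed off-app weeks already inform the prediction. With an indicator it is about zero. This pattern counts only if 10.4.1 is read to send such patients to the within-arm model.

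**The case against.** A reader might infer that every app-arm patient who stops the app is imputed as a continuing user. The documents do not support that. The main group with missing data after stopping, the study dropouts, is imputed from the control arm. Intervention dropouts contribute observed off-app weeks and also serve as donors. Larger shifts, 0.05 to 0.12 days, come out if 20 to 40% are non-adherent from week 6 or 9 with diary gaps inside that spell. Those patients, however, mostly fall under CIR or under the unsettled row of the table, and so many off-app patients who still document sits badly with the SAP's expectation that intervention dropouts will be few.

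The direction is also conditional. If the app has no effect there is no shift, so this mechanism does not create false positives. If benefit persists after stopping there is none either. SAP 10.4.1 reports that benefit had been seen among patients dropping out in earlier app data, and relaxation or exercise can continue without the app, so non-adherent need not mean untreated.

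Finally, an adherence coefficient would be estimated from non-adherent patients who still document, a group the SAP expects to be too small to impute from.

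The first two arguments stand and set the limits of this point. The third stands in part: 10.4.1 rejects imputing from intervention dropouts alone, whereas a covariate keeps every donor. It would still be imprecise if few such patients exist, above all among those with chronic migraine.

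**Conclusion.** The omission is real but its reach is small. It affects app-arm missing weeks outside CIR: late silent stoppers, off-app gaps of one to three weeks, and possibly long-term non-adherent patients with partly kept diaries. In the scenarios run, with 10 to 20% of the arm off the app, the confirmatory estimate moves by about 0.01 to 0.09 days in favour of the app. That is 0.01/1.27 = 0.8% to 0.09/1.27 = 7% of the planned effect, and 0.01/0.45 = 0.02 to 0.09/0.45 = 0.20 standard errors. The low end comes from a partly-kept-diary run with full loss of effect and would be about half that under half loss.

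The rates of stopping, the number of missing weeks and the loss of effect are all assumptions. The result also needs the app to work and its benefit to fade on stopping. The point does not threaten the trial's conclusion. It is a small, one-directional and avoidable shift in the primary analysis.

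**What to change.** - In SAP 10.4.3, add an off-app indicator (weekly non-adherence as defined in 6.3) to the predictors of the app-arm imputation model. Keep all donors and the rest of the model. If non-adherent documenters are sparse, pool the indicator over weeks and migraine type.
- In SAP 10.4.1, state whether patients who are non-adherent for four or more weeks with a partly kept diary are imputed by CIR or by the within-arm model.

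The cost is a few lines of text and one variable that is already logged. Imputations become somewhat noisier, and intervals slightly wider, if few non-adherent patients keep documenting.

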## 10.5 ANALYSIS FOR THE EFFECTIVENESS OF THE APP

### 10.5.1 Primary analysis of the primary outcome

The analysis for the primary endpoint (migraine days week 9-12) will be conducted using an analysis of covariance (ANCOVA) with the treatment group (intervention/control) as fixed factor and baseline migraine days (during 28 days) and type of migraine disease (chronic vs. episodic migraine = stratification variable during randomization) as covariates.

The analyses will be based on the ITT population and handling drop out and missing data are defined in chapter 10.4.

From the ANCOVA model, estimated means and 95% confidence intervals, standard errors and the p-value for the group comparison will be obtained. The significance level is set at 0.05 (two-sided).

### 10.5.2 Sensitivity analyses of the primary outcome

The analysis of the primary outcome as described in 10.5.1 will be repeated:

- for the ITT as described above using an extended ANCOVA that includes also those variables as covariates, where clinically relevant baseline differences between the two groups (M-sense Migräne app, control app) were observed,
- for the ITT replacing missing data for study dropouts using multiple imputations,
- based on the FAS population.

Furthermore, a GLM (repeated-measure ANCOVA) will be fitted to the data based on the ITT to compare the two groups (M-sense Migräne app, control app) with respect to changes in the number of headache days per month over time (using data on a weekly bases from week 1-12). The model will include the treatment (M-sense Migräne app and control app) and time as fixed main effects, an interaction term for treatment by time, and the baseline headache days as well as type of migraine disease (chronic vs. episodic) as covariates.

All sensitivity analyses for the primary outcome will be considered explorative.

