## 11.9 Further analyses

As supportive analysis models for repeated measures will be fitted to compare the groups with respect to changes in the primary outcome over time. Further details will be described in the SAP.

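### The repeated-measures model listed as a sensitivity analysis of the primary outcome is specified on headache days, so the plan has no joint longitudinal model of migraine days

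*Combined protocol and SAP*

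**What the plan says.** SAP 10.5.1 fixes the primary model: "The analysis for the primary endpoint (migraine days week 9-12) will be conducted using an analysis of covariance (ANCOVA"), with "baseline migraine days (during 28 days) and type of migraine disease (chronic vs. episodic migraine = stratification variable during randomization) as covariates". SAP 6.1 gives the same endpoint and obtains it through a blinded physician's classification of each headache attack.

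SAP 10.5.2 is headed "Sensitivity analyses of the primary outcome". It first repeats the 10.5.1 analysis in three ways: with extra covariates, with a different imputation for study dropouts, and on the full analysis set. It then adds a repeated-measures ANCOVA in the ITT population, comparing the groups "with respect to changes in the number of headache days per month over time (using data on a weekly bases from week 1-12"). That model has treatment, time and their interaction, with "the baseline headache days as well as type of migraine disease (chronic vs. episodic) as covariates". The section closes: "All sensitivity analyses for the primary outcome will be considered explorative".

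Evaluation concept 11.9 describes the supportive analysis differently: "models for repeated measures will be fitted to compare the groups with respect to changes in the primary outcome over time". It leaves the details to the SAP.

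**The concern.** The model's heading and its content name different variables. Both the outcome and the baseline covariate are headache days, so this does not look like one mistyped word. The SAP states in its sections 1 and 5 that it takes the place of the evaluation concept. A statistician following it would therefore fit the headache-day model, and the longitudinal analysis of the primary outcome described in evaluation concept 11.9 would not be done.

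Two things are at stake. The result would be filed among the sensitivity analyses of the primary outcome in the report to the regulator, which itself asked for migraine days as the endpoint (SAP 5 and 6.1). And if the mismatch is noticed only after unblinding, the choice between the two variables could be influenced by the results.

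**Working it through.** No figure in the plan carries this point, so the check is mainly a comparison of texts.

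**1. The plan's own figure.** The sample size in SAP 7 is built on migraine days.
- Pre-post change in the pilot data: 5.63 - 3.94 = 1.69.
- Control reduction: 0.25 × 1.69 = 0.4225, stated as 0.42.
- Difference: 1.69 - 0.42 = 1.27, with SD 4.20.
- Normal approximation: n per group = 2 × (1.96 + 0.84)² × 4.20² / 1.27², which rounds up to 172.
- The exact two-sided t-test gives 172.65, rounded up to 173 as stated. Power at 173 per group is 80.1%.

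The figure reproduces and does not depend on the repeated-measures model.

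**2. The specifications side by side.**

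| Place | Outcome | Baseline covariate | Period |
|---|---|---|---|
| SAP 10.5.1, primary ANCOVA | migraine days | migraine days | weeks 9-12 |
| SAP 10.5.2, three repeats of 10.5.1 | migraine days | migraine days | weeks 9-12 |
| SAP 10.5.2, repeated measures | headache days | headache days | weeks 1-12 |
| Evaluation concept 11.9, repeated measures | primary outcome | left to the SAP | over time |

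The third row disagrees with its own section heading and with the fourth row.

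**3. Are the two variables interchangeable?** No. SAP 6.2 counts a headache day whenever the patient documents a headache. SAP 6.1 sorts headache days into migraine (M), tension-type (T) and other (O). At day level H = M + T + O, so

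group difference in H = difference in M + difference in (T + O).

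The two effects are equal only if the app leaves T + O unchanged relative to control. Nothing in the documents gives T or O, so the gap cannot be computed. A headache-day count also bypasses two steps that produce the primary endpoint: the blinded classification (SAP 6.1) and the rule in SAP 10.4.3 that counts insufficiently documented headache days as migraine days. It cannot show whether the migraine-day result is stable over time under those steps.

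**4. Is there another joint model of migraine days?** SAP 6.2 and Table 2 give migraine days in weeks 1-4 and 5-8 an ANCOVA each. With the primary analysis, all three 28-day periods are estimated, but separately. No other listed analysis combines the weeks with a treatment-by-time term.

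**5. The unit.** The sentence names a monthly count but uses weekly data. A week holds 0-7 days and a month, as the plan defines it, 0-28, a factor of 28 / 7 = 4. The planning difference of 1.27 per 28 days is 1.27 / 4 = 0.3175, about 0.32, per week. A coefficient cannot be set beside the primary estimate until the scale is fixed.

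**The case against.** The strongest reply is that little depends on this model. SAP 9.1 makes only the primary analysis confirmatory, and 10.5.2 calls every sensitivity analysis exploratory. The model names headache days openly, so a careful reader would see which variable was used. Migraine days are a component of headache days, so the analysis is related to the endpoint. All of this stands, and it limits the weight of the point. It does not remove the conflict between SAP 10.5.2 and evaluation concept 11.9.

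Several stronger readings are tempting, and the documents do not support them:
- **That the robustness of the primary result goes untested.** Three of the four analyses in 10.5.2 repeat the migraine-day ANCOVA.
- **That the course of migraine days over time is never examined.** The separate ANCOVAs for weeks 1-4 and 5-8 examine it. Only a joint model is missing.
- **That the headache-day effect may differ greatly, or even in sign.** This is possible in principle, but no data in the documents bear on it.
- **That the revision history proves the text is left over from the former endpoint.** SAP 5 confirms that headache days were the earlier primary endpoint, and the list of sections changed with it omits 10.5.2. That fits a leftover, but it is an inference. The point rests on the current text alone.
- **That the model class is wrong and a mixed model is needed.** Nothing here shows the specified repeated-measures ANCOVA to be faulty. A change of class would also raise questions of covariance structure and of fit with the imputation in SAP 10.4.

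**Conclusion.** The point holds in a limited form. One exploratory analysis of four in SAP 10.5.2 is specified on the wrong variable for its heading, in both outcome and baseline covariate, and conflicts with evaluation concept 11.9. The consequence is that the plan contains no joint weeks 1-12 model for migraine days. The primary ANCOVA, its significance level and the 346 patients are untouched. It should be fixed because the text is wrong as it stands and easy to correct, not because the main conclusion is at risk.

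This assumes that 11.9 states what the model is for. If the sponsor did intend a headache-day model, it is in the wrong section and the analysis described in 11.9 is missing.

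**What to change.** In the repeated-measures paragraph of SAP 10.5.2:

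1. Make migraine days the outcome in place of headache days.
2. Make baseline migraine days the covariate in place of baseline headache days. Keep migraine type, treatment, time and the interaction as they are.
3. State one unit. If weekly counts are modelled, call them weekly and say how estimates are converted to 28 days for comparison with the primary result. State the unit of the baseline value as well.

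If a longitudinal headache-day model is still wanted, list it under SAP 10.5.4 and Table 2 with the other headache-day analyses. Evaluation concept 11.9 needs no change.

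The cost is two phrases and a statement of the unit, made in a dated SAP revision before unblinding. The daily diary already supplies the data, and SAP 10.4.3 already imputes the diary by week. Data collection, sample size and patient burden do not change.
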